### Process evaluation

A process evaluation will be undertaken to determine whether the intervention is delivered as intended. Treatment fidelity is the strategy used to monitor and enhance the reliability and validity of interventions. This evaluation will address important questions regarding GP decision-making on treatment escalation. It may not always be appropriate to escalate treatment in the context of multimorbidity and other patient-related factors, and data on decision-making will be collected, whether treatment escalation occurs or not.

The process evaluation will include qualitative analysis and quantitative measures of treatment fidelity, collected through the website activity as part of the DECIDE treatment algorithms [41]. Qualitative methods will be used to explore the GP’s experience of participating in and delivering the DECIDE intervention. Semi-structured interviews (by MM) will be conducted with each participating GP. The collection of data will take place during the intervention and at 2 months after intervention completion, interviewing GPs and practice nurses from participating practices. Interviews will be conducted using telephone or in person and will be audio recorded. The topic guide will include the context to the intervention, fidelity and implementation and participant experiences. A thematic analysis will be conducted using normalisation process theory, to understand how the intervention was embedded in routine clinical practice [42]. NVivo will be used to organise and index the data.

### Health economic analysis

A preliminary health economic analysis will be conducted to compare the alternative treatment strategies: (1) *intervention*, DECIDE intervention plus usual GP care, and (2) *control*, versus usual GP care alone. The evaluation will identify, measure, value and compare the costs and outcomes of the alternatives being considered. A healthcare perspective will be adopted with respect to costing with a range of health service contacts recorded and valued, including GP use, hospital admissions, attendances at outpatient clinics and emergency clinics, and drug prescriptions. In addition, a micro-costing process will be undertaken to capture resource use relating to the operation and delivery of the DECIDE intervention. Unit costs will be applied to convert data on resource use to resource costs, and total cost variables will be calculated for both arms. For the exploratory analysis of cost effectiveness, data on total costs and the primary outcome measure of the HbA1c will be employed in an incremental analysis to explore the mean differentials in costs and effects between the intervention and the control. Univariate and multivariate sensitivity analyses, in addition to cost effectiveness acceptability curves, will be employed to address the uncertainty in the study. The output from the pilot study will provide information on the potential costs and cost effectiveness of the intervention, as well as the feasibility and acceptability of the proposed health economic approach and analysis plan, which will inform the design of a definitive RCT to evaluate its expected cost effectiveness in the future.

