Pilot component	Issue identified in non-randomised feasibility study	Change for future pilot cluster randomised controlled trial
DECIDE finder tool	Extension of utilisation to other electronic health records (EHRs) (beyond the Socrates EHR)	A bespoke Finder Function to enable practices utilising other EHRs was developed.
DECIDE CDSS and treatment escalations options	The three domains of suggested intensification options (glycaemic, anti-hypertensive and lipid-lowering medications) were appropriate, and the CDSS was deemed useful to prompt GPs on what evidence-based intensification options were available.	Not applicable.
Non-pharmacological options	Therapeutic intensification actions were deemed not possible in approximately one third of patients, due to complex social reasons.	The DECIDE intervention actions were comprised of three intensification options for glycaemic, BP and lipid-lowering medications. A forth option—providing options of non-pharmacological actions—was added to the intervention. Examples of non-pharmacological actions included referral to a community-based diabetes nurse specialist, asking for more frequent reviews and contacts with the patient or calling the patient in for another review to discuss compliance.
Follow-up of patients	Some patients with poor control were found to have significant care needs, which would require more frequent review.	An increase in the frequency of structured visits for these persons, through individualised reviews, was recommended. Though this is a contractual matter for the GPs concerned in terms of the provision of diabetes care, the DECIDE intervention was modified to enable multiple reviews—not just one review every 6 months.
Introductory educational information on the DECIDE website, in the educational videos and DECIDE practice folder	The educational information in the DECIDE folder was deemed useful.	Some minor additions to this folder, to include the above information, were added.

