### Population

GPs will be the target of the intervention and will be the unit of randomisation (the clusters).

Patients with poorly controlled T2DM will be targeted by the GP with the DECIDE intervention. All included patients must have a diagnosis of T2DM, identified by the finder tools in the EHR (discussed above). They must be aged over 18 years and less than 75, as there is less evidence about treatment intensification in patients aged above 75 years. However, patients with both a HbA1c > 70 mmol/mol and a BP > 150/ 95 mmHg will be recruited initially to the study, followed by those with an elevated HbA1c if the total number of patients with both risk factors poorly controlled is less than ten, followed by those with just elevated BP. Not all patients will be suitable for treatment intensification, and individual decisions on treatment changes will be made and recorded by each patient’s GP.

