### Data analysis

Practice and patient-chart information will be collected. Baseline data from the practice (cluster units) will be collected prior to allocation using a practice-based questionnaire. Patient-level outcomes will be collected after allocation, using the DECIDE website, inputted by the practice nurse, then general practitioner and anonymised at practice level. Due to the nature of the project and targeting of the intervention at cluster level, patient-reported outcome measures will not be collected, as this would be beyond the scope of the proposed project and would require individual patient consent.

All results will be collected at practice level by uploading anonymised patient data through the web-based DECIDE system. Patient data is recorded at the individual level. Initially, appropriate descriptive statistics (for example, means (SD), medians (IQR) and frequencies and percentages) will be used to assess balance between the intervention and control for both practice and patient characteristics. Descriptive statistics will also be used to assess measures of feasibility such as recruitment and retention of practices.

Mixed effects regression models will be used to account for the hierarchical nature of the data. The primary analysis is to estimate HbA1c for the intervention group versus the control, adjusting for baseline HbA1c and minimisation factors. A random effects linear regression will be used, including a random practice effect to account for the correlation between patients in practices. In a secondary analysis, we will further adjust for any variables displaying an imbalance between groups at baseline. Both intention to treat (i.e. including all randomised practices and patients, regardless of participation in the intervention) and per protocol analysis (to explore whether adherence to the intervention influences the effect of the intervention) will be conducted.

The above analyses will be repeated for secondary outcomes (BP, lipids), healthcare utilisation (including practice and hospital visitation rates) and medication intensification. All analyses will use appropriate (that is, logistic or linear) regression models, with results presented as point estimates (odds ratios or difference in means), 95% confidence intervals and *p* values. The primary analyses will involve intention-to-treat comparisons between the two groups, and a secondary per protocol analysis will also be conducted [39].

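### The exploratory cost-effectiveness analysis sets total cost, with drugs of every class, against HbA1c alone, although DECIDE also prompts blood pressure and lipid treatment

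*Protocol article*

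**What the plan says.** The Health economic analysis section takes a healthcare perspective. It values a range of service use, "including GP use, hospital admissions, attendances at outpatient clinics and emergency clinics, and drug prescriptions", adds a micro-costing of DECIDE delivery, and states that "total cost variables will be calculated for both arms". On the effect side it names one measure: "data on total costs and the primary outcome measure of the HbA1c will be employed in an incremental analysis". Uncertainty is to be handled by "Univariate and multivariate sensitivity analyses, in addition to cost effectiveness acceptability curves", whose content is not described.

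Table 3, in the section on development and the feasibility study, describes what DECIDE prompts: "The DECIDE intervention actions were comprised of three intensification options for glycaemic, BP and lipid-lowering medications", with a fourth, non-pharmacological option added. The Population section recruits first those with both HbA1c and blood pressure raised, then those with raised HbA1c, "followed by those with just elevated BP". Blood pressure and lipids are analysed as secondary outcomes under Data analysis, but the economic section does not mention them. Under Continuation criteria, one of five considerations is whether the exploratory economics suggest that DECIDE may be cost effective.

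**The concern.** The scope of the costs is wider than the scope of the effect. Two of the three drug classes that DECIDE promotes can enter the cost side, while their intended effects have no place on the effect side. The more DECIDE succeeds in prompting blood pressure and lipid treatment, the less favourable its cost per unit of HbA1c looks.

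The result has two uses. It feeds a continuation criterion, and the pilot is also meant to try out the economic approach for the definitive trial, so a one-sided comparison could be carried forward.

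**Working it through.** The documents give no unit costs, expected cost difference or cost-effectiveness figure, so there is no plan figure to reproduce. The check is first structural, then illustrative.

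**1. Scope of cost against scope of effect**

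| Domain prompted by DECIDE (Table 3) | In total cost? | In the effect measure? |
|---|---|---|
| Glucose-lowering drugs | Yes | Yes, HbA1c |
| Antihypertensive drugs | Yes, prescriptions not limited by class | No |
| Lipid-lowering drugs | Yes, same | No |

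**2. Could the missing effects enter elsewhere?**
- A generic outcome: Data analysis rules out patient-reported measures, so no questionnaire-based one is available.
- Cost savings: avoided admissions and emergency visits would lower total cost. Follow-up is 3 months after the intervention window (Data collection) or 4 months after the intervention finishes (Trial process). Added drug cost accrues at once; little vascular benefit could show in that time.
- Sensitivity analyses: they might address the point, but nothing says that they will.

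**3. Direction**
Write incremental cost as ΔC = ΔC_rest + ΔC_BL, where BL is blood pressure and lipid drugs, and the effect as ΔE, the HbA1c reduction. At a value λ per mmol/mol, net benefit is λΔE − ΔC. These drugs are not aimed at HbA1c, so ΔC_BL > 0 lowers net benefit by ΔC_BL at every λ and moves the acceptability curve down. If blood pressure and lipid prescribing does not rise, there is no such shift.

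**4. Size, under an assumed share**
Let s = ΔC_BL / ΔC, with ΔC > 0, ΔE > 0 and s between 0 and 1. Then

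(ΔC/ΔE) ÷ (ΔC_rest/ΔE) = 1/(1 − s).

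| Assumed s | 1/(1 − s) |
|---|---|
| 5% | 1/0.95 = 1.05 |
| 10% | 1/0.90 = 1.11 |
| 20% | 1/0.80 = 1.25 |
| 50% | 1/0.50 = 2.00 |

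The share must be of total incremental cost, not of drug cost alone. If blood pressure and lipid drugs are a share x of incremental drug cost, and drugs are a share d of incremental cost, then s = xd. With x = 20% and d = 25% (both assumed), s = 5% and the factor is 1.05. With x = 40% and d = 25%, s = 10% and the factor is 1.11. Only if drugs were the whole incremental cost (d = 100%) would x = 20% give 1.25.

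**5. Is extra prescribing plausible?**
Table 2 (37 patients) shows 9 + 13 = 22 on no antihypertensive or one (22/37 = 59%) and 10 on no lipid-lowering drug (10/37 = 27%). The same sample had mean blood pressure 140.9/83.4 mmHg and mean total cholesterol 4.7 mmol/L, and therapeutic intensification was judged not possible in about a third. The table shows that some extra prescribing is possible, but not how much.

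**The case against.** The strongest reply is that this is a disclosed and recognisable choice. Total cost is what a healthcare perspective calls for, HbA1c is the only clinical primary outcome, and the analysis is labelled preliminary and exploratory. The article speaks of mean differentials rather than a ratio, and it leaves the sensitivity analyses open, as articles often do. The continuation criteria centre on feasibility, set no threshold per mmol/mol, and separately count medication intensification without limiting it by class.

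Most of this stands, and it rules out several stronger readings that a reader might infer:

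- *Total cost is the wrong numerator, and blood pressure and lipid drugs should be taken out of the main comparison.* The stated perspective bears those costs and DECIDE prompts them. Removing the drugs while keeping all service contacts would create a new mismatch, tilted towards DECIDE.
- *The bias is known to be large.* No costs are given, and Table 2 does not show how much intensification is needed.
- *Recruitment favours blood pressure.* The first tier must also have raised HbA1c, and blood-pressure-only patients come last. The feasibility section even reports a decision to target only raised HbA1c, which does not sit with the Population section. The mismatch does not depend on that, because the three drug options are not confined to any tier.
- *A continuation decision will turn on it.* No stated rule does.

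What the reply does not remove is the single effect measure. Analysing blood pressure and lipids elsewhere does not bring them into the economic comparison, and an incremental analysis with acceptability curves makes the same comparison as a ratio.

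**Conclusion.** The point holds as a mismatch of scope, not as an error in costing. If DECIDE raises blood pressure and lipid prescribing, as its design intends, the HbA1c-only comparison is tilted against it. The factor 1/(1 − s) is illustrative and rests on an assumed s, a positive incremental cost and an HbA1c benefit; the documents cannot narrow it. The conclusion also takes the unrestricted reference to drug prescriptions to cover all three classes, which is the natural reading but is not spelled out.

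This is a cheap improvement worth making before the economic result is read for continuation or for the definitive trial. It does not invalidate the pilot.

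**What to change.** 1. Keep total cost against HbA1c, with its acceptability curve, under the healthcare perspective.
2. Add a cost-consequence table: incremental cost by component (DECIDE delivery; glucose-lowering, antihypertensive and lipid-lowering drugs; service contacts) beside the between-arm differences in HbA1c, systolic and diastolic blood pressure, and lipids, each with a 95% confidence interval.
3. Under Continuation criteria, say that the economic item is judged on that table together with the HbA1c analysis.
4. If a costing limited to glycaemic care is wanted, report it only as a labelled sensitivity analysis, and state that it drops costs within the chosen perspective.

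The cost is wording in two sections and one extra table from data already collected; no new consent or sample size is needed. The downside is that the economic criterion no longer rests on a single comparison and needs judgement across several outcomes.

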### Continuation criteria

We will use continuation criteria to assess if further evaluation of this intervention is warranted, through a formal RCT. The criteria for continuation will be based around feasibility. We will use quantitative and qualitative process evaluation data to consider the following:Successful recruitment and retention of 14 general practices and of patients with poor control of T2DMImplementation of the intervention as plannedAcceptability of the intervention for GPs as per the process evaluationPotential effect on patient’s glycaemic control and medication intensificationExploratory economic analysis indicates that the intervention could be cost effective

### Ethics and data management

Ethical approval has been granted by the ICGP Research Ethics Committee.

A study steering committee will agree on the final data management plan. Currently, the data received from practices (collected by recruited GPs) will be completely anonymised. A unique study identifier number will be given to each GP by the study team, to record each patient participant (this will be recorded in the data collection tool for baseline data measurement). On follow-up, intervention GPs will use the unique patient ID to input the outcome data. Qualitative evaluation data from intervention GPs will be collected through semi-structured interviews which will be audio recorded and transcribed. All practice and anonymised patient data will be stored on secure password-protected hard drives and transferred to a secure password-protected server. Hard copies of data (i.e. completed questionnaires and practice consent forms) will be scanned and stored electronically on a secure password-protected server in accordance with data protection policies; the original copies will be shredded.

## Discussion

Poorly control T2DM is a major contributor to both morbidity and mortality of patients and increasing economic costs [1]. Few professionally targeted interventions have been developed, which specifically focus on patients with poor control of T2DM [26]. Similarly, there is limited evidence on the effect of interventions, which aim to support the intensification of medications and address clinical inertia in T2DM management. We have reported the findings of a non-randomised feasibility study of a complex intervention, which aims to support GP-based management of poorly controlled T2DM. A web-based CDSS, called the DECIDE intervention, was developed to support evidence-based prescribing for patients with poorly controlled T2DM. The non-randomised feasibility study showed that focussing on the medication intensification in poorly controlled T2DM in general practice is suitable, but should also consider non-pharmacological intensification options, such as more frequent reviews and referral to other healthcare professionals. We have then reported the protocol for a cRCT, which aims to assess the feasibility of a DECIDE study. If the study is feasible and the trial methodologies are robust, we will aim to proceed to a full cluster RCT. With the prevalence of diabetes rising globally to 422 million affected adults in 2014, compared to 108 million in 1980, the need for interventions to address the causes of poor control of diabetes are warranted—especially for a cohort of patients who are especially vulnerable to the effects of micro- and macro-vascular complications of poorly controlled T2DM [1]. DECIDE will also not focus on aggressive reductions in HbA1c on those with moderate control to T2DM, aiming to reduce the potential for harm in borderline populations [24–26].

Limitations of the study include the potential that the use of the finder tool in the control practices could contaminate this group and promote a heightened attention on the identified patients. However, we will ask that the finder tool be run by practice nurses only and none of the educational or CDSS elements (e.g. the DECIDE folder or website training) will be available to control practices so treatment will continue as usual. The patients in the control group will continue to receive usual care, which is a six monthly review in the practice. Control practices will be offered access to the DECIDE intervention following study completion. We plan on performing a process evaluation, which will also identify if contamination occurs. Prescribing is a very complex task—especially for patients with poorly controlled T2DM who may also have complex social needs [6]. Though prescribing options are complex in the CDSS, the feedback from the non-randomised feasibility study was that intensification suggestions were logical and not over-burdensome for the intervention GPs. As the reasons for poor control can be multi-faceted and complex, the requirement to address non-pharmacological intensifications options was identified through the non-randomised feasibility study and these options will be provided to intervention GPs in the cRCT.

In summary, DECIDE aims to support GPs in Irish Primary Care to intensify medications, where appropriate, for patients with poorly controlled T2DM, mediated through a complex intervention comprising a CDSS and an educational component.

## Abbreviations

BP: Blood pressure
CDSS: Clinical decision support system
CONSORT: Consolidated standards for Reporting Trials
DECIDE: ComputeriseD dECisIonal support for poorly controlleD typE 2 Diabetes mellitus in Irish General Practice
EHR: Electronic health record
GP: General practitioner
HRB: Health Research Board
ICC: Intra-cluster coefficient
ICGP: Irish College of General Practitioners
NICE: National Institute for Health and Clinical Excellence
T2DM: Type 2 diabetes mellitus
